#### Preservation and disposal of human remains.

All human remains will be preserved and disposed of in accordance with Article 39 of the Act on Bioethics and Safety.

Upon withdrawal of consent to participate in the study or termination of the study, all stored human remains will be classified as medical waste and incinerated, and records related to the disposal (date, amount, method of disposal, etc.) will be kept for 5 years from the date of disposal.

### Serum Analysis (Serum)

Blood collected from cancer patients will be clotted for 30 minutes at room temperature, centrifuged at 1000 × g for 20 minutes to separate the serum only, and stored at −80°C.The serum will be used to measure the expression of factors associated with cancer cell growth (Trim63, Fos, Col1a, and Six2) that have been identified in cell experiments in our laboratory [21]. The cancer development-related markers Human Trim63 (HUF105955; Assay Genie, Dublin, Ireland), Human FOS (HUF101186; Assay Genie), Human Pro-Col1a1 (R&D Systems, Minneapolis, MN, USA), and Human Six2 (ABIN6232377; Antibodies Online, Limerick, PA, USA) will be analyzed using ELISA kits. Additionally, blood will be collected to assess inflammation levels using the Human C-Reactive Protein/CRP Immunoassay (SCRP00B; R&D Systems).

Randomization and exercise intervention adjustment

After enrollment in the study, all participants will be enrolled in a study-specific app (Fig 2), where they will enter baseline fitness measurements and heart rate data. Based on this, an exercise specialist will adjust the exercise intensity for each subject to provide the appropriate intervention.

**Fig 2 pone.0327947.g002:**
[figure not shown]
A study-specific app.

In this study, the information provided to the exercise intervention group and control group will be different and blinded to ensure that the information is balanced. The exercise intervention group will be provided with a structured exercise program, and they will adjust their own exercise intensity based on their training (Fig 3).

**Fig 3 pone.0327947.g003:**
[figure not shown]
Diagram algorithme.

To evaluate the effectiveness of the exercise intervention, all participants will be measured three times. Data will be de-identified with a numeric code per subject and managed so that only the principal investigator will have access to all participants’ identifying information.

2Exercise interventions

The study will be a 3-month, parallel-group, randomized controlled trial consisting of cancer patients (100) and non-cancer patients (300). The cancer patient group will consist of patients undergoing treatment or post-operative rehabilitation, while the non-cancer patient group will include subjects at more than twice the risk of developing the disease, members of exercise centers, and those who only use ICT apps.

The cancer patient group will be provided with a tailored exercise program to improve cardiorespiratory fitness and muscle strength, which will aim to improve physical function and quality of life.

The **EXESALUS program** is designed so that participants start the exercise intervention within 10 days of enrollment, once their health risk results are confirmed through genetic testing.

If a subject is unable to start the exercise intervention, it will be recorded as a ‘protocol intervention withdrawal.’

Psychological counseling by a clinical psychologist will be provided twice, once before starting the exercise intervention and again at 2-months, to ensure study participation and ongoing motivation.

3-1EXESALUS Exercise Program

The EXESALUS exercise program (http://exesalus.com) is an ICT-based personalized exercise intervention program for health promotion and disease prevention (Fig 4). The program provides a variety of exercises targeting the upper body, lower body, abdomen, and whole body (adjusted by intensity) and provides five workouts per week for 3 months, ranging from low to high intensity, using exercises that are appropriate for the target audience. The goal is to build muscle strength and improve psychological well-being.

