**Methods:**

This is a protocol for a 3-month, parallel-group, randomized controlled trial involving 500 participants, including 100 cancer patients undergoing treatment or rehabilitation and 300 non-cancer participants with elevated disease risk. Participants will engage in the EXESALUS program, which includes low-, moderate-, and high-intensity exercise tailored to genomic profiles, supported by exercise counseling and wearable device feedback. Biospecimens (blood, urine, and oral epithelial cells) will be collected at baseline, 6 weeks, and 3 months to assess genomic variations and physiological changes. Primary outcomes include physical performance (SPPB), muscle strength (1RM and peak power), and skeletal muscle mass (DXA). Secondary outcomes will evaluate mental health indicators such as fatigue (FACIT-F), resilience, anxiety, depression, and quality of life.

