### Subject selection criteria and methods

Subjects will be selected based on the following criteria:

300 registered participants of the Health and Exercise Center who participate in exercise at least once a week and voluntarily agree to participate in the study.100 patients registered at Yeungnam University Medical Center.100 members of the general public who do not participate in exercise.

The total number of subjects is set at 500 for the 3-month study period, and the study will be conducted on subjects who agree to participate after being provided information about the study. Written informed consent will be obtained after the exercise specialist confirms that the subject meets the requirements for participation.

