**Fig 6 pone.0327947.g006:**
[figure not shown]
Exercise motions.

The exercise program begins with a light-intensity warm-up session that focuses on flexibility and includes balance exercises customized for each participant. The program consists of warm-up, stretching, and cool-down sessions, and utilizes smartwatches to provide real-time biometric feedback. Unlike traditional exercise programs, EXESALUS has a unique advantage in that it provides high-intensity exercise that is effective in stimulating lymph nodes and lymph glands in cancer prevention and management.

Studies have shown that as physical health improves, cognitive and psychological functioning also shows positive changes. However, the optimal level of exercise intensity and frequency is still being researched. EXESALUS offers a program that consistently delivers low-, medium-, and high-intensity workouts based on proven benefits. Under the guidance of an exercise physiologist without financial burden for 3 months, subjects are guided to perform high-intensity exercise through a customized program (figure diagram algorithm).

3-2Control group

The non-exercise group will consist of subjects whose risk of developing the disease is 2 or less according to the genetic test.

At the beginning of the intervention, wearable devices and setup assistance will be provided, and the wearable devices will be distributed to 100 subjects.

During the study period, the control group will maintain their daily routine without any specific exercise intervention while self-monitoring using the provided wearable devices. This will allow us to observe and compare changes in the health status of the control group.

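### The trial is described as 400 participants in one section and 500 in another, and the 300 non-cancer participants and the control group are defined differently from section to section

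*Protocol article*

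**What the plan says.** Four places in the protocol article describe who is in the trial.

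- **Abstract, Methods:** a trial "involving 500 participants, including 100 cancer patients undergoing treatment or rehabilitation and 300 non-cancer participants with elevated disease risk".
- **Subject selection criteria and methods:** three strata, namely "300 registered participants of the Health and Exercise Center who participate in exercise at least once a week", "100 patients registered at Yeungnam University Medical Center" and "100 members of the general public who do not participate in exercise". The total is fixed at 500. No stratum carries a genetic-risk criterion.
- **Section 2, Exercise interventions:** "The study will be a 3-month, parallel-group, randomized controlled trial consisting of cancer patients (100) and non-cancer patients (300". It adds that the non-cancer group takes in people with more than double the disease risk, exercise-centre members and app-only users.
- **Section 3-2, Control group:** the non-exercise group is made up of people whose genetic test puts their disease risk at 2 or less. They keep their usual routine and monitor themselves. No number of controls is given, but "wearable devices will be distributed to 100 subjects".

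The section Rationale for subject selection also mentions about 400, as the number expected to remain from 500 after non-response and dropout.

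**The concern.** Total, composition, entry criterion and comparator are core protocol content, and here they depend on the section that is followed. Three things are at stake.

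1. **Count.** A reader cannot tell whether the randomized set is 400 or 500, or whether the non-exercising members of the public belong to it.
2. **Population.** The abstract leads a reader to apply the result to non-cancer people at raised risk. The selection criteria recruit on gym attendance instead.
3. **Comparator.** A group called non-exercise, but defined by a risk score, can include people recruited because they exercise every week. If habitual exercise affects strength, muscle mass or physical performance, such controls shrink the difference between arms. The comparison then becomes the EXESALUS program against habitual exercise rather than against no exercise.

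If these points stay open until the data are in, the population and the comparator could be chosen after results are known.

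**Working it through.** **Step 1: reproduce the stated total.** Inputs are the three strata in Subject selection criteria and methods.

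300 + 100 + 100 = 500, which matches the total given there.

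**Step 2: repeat with section 2.** Inputs are the two numbers in its opening sentence.

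100 + 300 = 400. Shortfall: 500 − 400 = 100, and 100 / 500 = 20%.

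The sentence is worded as a full description of the trial, so it does not leave room for a further group.

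**Step 3: locate the missing 100.** Two of the three strata have matching sizes in section 2 (100 and 300). The stratum left over is the 100 non-exercising members of the public. Adding it restores the total: 100 + 300 + 100 = 500.

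Assume that the 100 medical-centre patients are the 100 cancer patients; the selection criteria do not mention cancer. The non-cancer number is then 300 + 100 = 400, against the 300 in section 2. So adding the stratum repairs the total but not the stated number of non-cancer participants.

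**Step 4: test whether 400 means completers.** The rationale section expects about 400 of 500 to remain, a loss of (500 − 400) / 500 = 20%. The number is the same, but section 2 gives it as the make-up of the trial, with cancer and non-cancer counts equal to planned strata sizes. It is not presented as a number after dropout.

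**Step 5: set the descriptions of the 300 side by side.**

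| Place | Who the 300 are | Risk criterion |
|---|---|---|
| Abstract, Methods | Non-cancer participants | Raised risk, all |
| Subject selection criteria | Exercise-centre members, at least weekly exercise | None |
| Section 2 | Raised-risk subjects, centre members, app-only users | Some |

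Weekly exercise at a centre and raised genetic risk are different criteria. A person can meet both, either or neither, so no two rows define the same group.

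**Step 6: apply the control rule to the recruited strata.** Section 3-2 sends everyone with a risk of 2 or less to the non-exercise group. Take a centre member who exercises weekly and has a risk of 2 or less:

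- eligible under the selection criteria;
- not at raised risk, so outside the abstract's description of the 300;
- a control under section 3-2, told to keep a routine that includes exercise;
- plausibly active under the active or not-active split in the Statistics section.

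The number of such people cannot be calculated. No share above or below 2 is given, and the disease in question is not named. The text sets only a ceiling of 300, the whole stratum.

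**The case against.** The strongest defence is that the missing 100 can be found. Section 2 is headed as the intervention section, and controls have their own subsection. That subsection mentions 100 wearables, and the selection criteria recruit exactly 100 people who do not exercise. A natural reading is 400 intervention participants plus 100 non-exercising controls. This is plausible, and a reader who infers that 100 people have no place in the design goes too far. But no section states the link, section 2 describes the whole trial, and section 3-2 defines controls by risk rather than by membership of that stratum.

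Other parts of the defence stand:

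- The abstract introduces its 100 and 300 as examples within 500, so on the count it is incomplete rather than contradictory.
- A reader might infer a shortage of wearables. The documents do not support that: no control headcount exists to compare with 100 devices, and 100 fits the non-exercising stratum.
- A reader might assume a share above risk 2 and derive arm sizes. Nothing in the article supports any particular share.
- A reader might infer that the trial can say nothing about people at elevated risk. That is too strong, since centre members may also be at raised risk and section 2 names such people. What is shown is an unclear entry criterion.

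The algorithm figure and the ethics-approved study plan are not shown and may set out the flow by arm. They could tell the authors which statement is right, but the conflicting statements in the article would still need correction.

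**Conclusion.** The point holds as an internal contradiction in population and comparator.

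- **Count:** 400 in section 2 against 500 in the selection criteria. One stratum of 100 (20% of 500) is omitted from section 2. The further mismatch of 400 against 300 non-cancer participants rests on the assumption that the medical-centre patients are the cancer patients.
- **Population:** the 300 have three descriptions that do not coincide, and the elevated-risk label in the abstract is not backed by the selection criteria.
- **Comparator:** the control rule permits weekly exercisers in the non-exercise group. The direction of the effect is dilution, provided that habitual exercise influences the outcomes. Its size cannot be given from the documents.

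The conflict between allocation by risk score and the claim of randomization is a larger matter. It enters here only because it leaves the control group undefined. This is a correction that should be made. It does not show that the trial cannot answer its question.

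**What to change.** Reconcile the abstract, the subject selection criteria, section 2 and section 3-2 as follows.

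1. Put one table in the design section, with strata as rows (exercise-centre members 300, medical-centre patients 100, general public 100) and randomized arms as columns, summing to 500. State whether the medical-centre patients are the cancer patients, and where the 100 non-exercising members of the public belong.
2. Replace the elevated-risk wording in the abstract with the entry criterion actually used, and report the share above risk 2 as an observed baseline variable.
3. Define control by randomized arm, not by risk score or exercise habit. Describe control participants' usual activity as it is, rather than calling the group non-exercise.

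**Cost.** Mostly wording in the protocol and abstract, and in the registry entry if it carries the same text (not available here). The scientific price is a narrower elevated-risk claim. It is a wording change only if participants are in fact being randomized; the article does not allow that to be checked. Recruitment is planned to finish by February 28, 2026, and the table should be fixed before any outcome data are analysed.

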**Fig 4 pone.0327947.g004:**

EXESALUS icon.

The EXESALUS app, designed to help prevent cancer and recurrence, slow muscle loss, and improve physical function, is accessible on mobile or PC (Fig 5) and features 3D customizable animations (Fig 6) and personalized avatars.

**Fig 5 pone.0327947.g005:**
[figure not shown]
Launcher icon.

**Fig 6 pone.0327947.g006:**
[figure not shown]
Exercise motions.

The exercise program begins with a light-intensity warm-up session that focuses on flexibility and includes balance exercises customized for each participant. The program consists of warm-up, stretching, and cool-down sessions, and utilizes smartwatches to provide real-time biometric feedback. Unlike traditional exercise programs, EXESALUS has a unique advantage in that it provides high-intensity exercise that is effective in stimulating lymph nodes and lymph glands in cancer prevention and management.

Studies have shown that as physical health improves, cognitive and psychological functioning also shows positive changes. However, the optimal level of exercise intensity and frequency is still being researched. EXESALUS offers a program that consistently delivers low-, medium-, and high-intensity workouts based on proven benefits. Under the guidance of an exercise physiologist without financial burden for 3 months, subjects are guided to perform high-intensity exercise through a customized program (figure diagram algorithm).

3-2Control group

The non-exercise group will consist of subjects whose risk of developing the disease is 2 or less according to the genetic test.

At the beginning of the intervention, wearable devices and setup assistance will be provided, and the wearable devices will be distributed to 100 subjects.

During the study period, the control group will maintain their daily routine without any specific exercise intervention while self-monitoring using the provided wearable devices. This will allow us to observe and compare changes in the health status of the control group.

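### The trial is labelled randomised, but its control group is defined by a genetic risk result, so exercise versus control is confounded with genetic risk and with cancer status

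*Protocol article*

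**What the plan says.** All references are to the protocol article.

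- **Design label.** The Exercise interventions section states: "The study will be a 3-month, parallel-group, randomized controlled trial consisting of cancer patients (100) and non-cancer patients (300". The Methods part of the Abstract uses the same label.
- **Who is a control.** Section 3-2 (headed Control group) says: "The non-exercise group will consist of subjects whose risk of developing the disease is 2 or less according to the genetic test". These people keep to their usual routine and monitor themselves with a wearable device. The same section says that devices go to 100 subjects.
- **Who exercises.** For cancer patients, the Exercise interventions section says: "The cancer patient group will be provided with a tailored exercise program to improve cardiorespiratory fitness and muscle strength". It describes the make-up of the non-cancer side in these words: "include subjects at more than twice the risk of developing the disease, members of exercise centers, and those who only use ICT apps". In the Abstract, this group is described as "300 non-cancer participants with elevated disease risk".
- **Timing.** The programme starts within 10 days of enrolment, "once their health risk results are confirmed through genetic testing". The genetic result is therefore known before exercise begins.
- **The paragraph that names randomisation.** Under "Randomization and exercise intervention adjustment" the text covers app enrolment, entry of baseline measurements and the setting of exercise intensity.

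**The concern.** Random allocation means that chance alone decides who is a control. A rule that fills the control group according to a genetic test result is selection on a baseline characteristic. The label and the rule cannot both describe the same comparison.

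If the rule is followed, controls differ systematically from exercisers in genetic risk, and none of them is described as a cancer patient. The Introduction says that genetic findings will be used to motivate exercise, so knowing one's result may also change behaviour. A between-group difference in SPPB, strength, muscle mass or fatigue could then reflect risk status, disease and treatment course, or knowledge of the result, as well as the programme. The Discussion nonetheless anticipates that the results will confirm significant effects in cancer patients. A reader who trusts the randomised label would take such a difference as causal.

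**Working it through.** **Step 1. The label against the rule.**

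| Participants | Assigned to, as written | Comparator described |
|---|---|---|
| Cancer patients (100) | Tailored exercise programme | None |
| Non-cancer, more than twice the risk | Non-cancer group, not in the control definition | None at the same risk |
| Exercise-centre members and app-only users | Non-cancer group, risk not stated | Unclear |
| Risk 2 or less | The non-exercise group is drawn from here | Not applicable |

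The only stated rule for membership of the control group is the genetic result. No cancer control and no high-risk control is described.

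**Step 2. What the article gives in numbers.** There is no stated figure for arm sizes to reproduce. The Rationale for subject selection gives 500 recruited and about 400 at the end, a loss of 100/500 = 20%. The stated sample-size inputs (power 0.8, effect size 0.5, alpha 0.05) do not lead to 500. For two equal arms and a two-sided test, n per arm = 2 × (1.960 + 0.842)² / 0.5² = 62.8, rounded up to 63. That is 126 in total, or 126/0.8 = 157.5, rounded up to 158, after 20% loss. This is a separate matter, and nothing below depends on it.

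**Step 3. Illustration of the consequence.** These inputs are assumptions:

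- Controls: 100, inferred from the 100 wearable devices; after 20% loss, 80.
- All others: 400; after 20% loss, 320.
- True programme effect: zero.
- Background difference in mean change between the groups: b SD. The documents give no value, so a range is shown.

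Standard error = √(1/320 + 1/80) = √0.015625 = 0.125 SD.

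Rejection rate of a nominal two-sided 5% test = Φ(b/SE − 1.96) + Φ(−b/SE − 1.96).

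| b (SD) | b/SE | Rejection rate |
|---|---|---|
| 0 | 0 | 5% |
| 0.1 | 0.8 | 12.6% |
| 0.2 | 1.6 | 36% |
| 0.3 | 2.4 | 67% |
| 0.5 | 4.0 | 98% |

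With the same 400 split 200 versus 200, SE = √(1/200 + 1/200) = 0.1 SD, and the rates for b = 0.1, 0.2, 0.3 and 0.5 become 17%, 52%, 85% and 99.9%. Greater precision does not remove the bias; it makes a false finding more likely.

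The illustration concerns programme versus control. The Statistics section instead groups participants as active or not active, which is not an allocated arm either.

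**The case against.** A journal article condenses the full protocol. The algorithm in Fig 3 and the ethics-approved study plan are not visible here, and a random step within part of the sample is conceivable. This stands to a point: the lack of any allocation procedure under the randomisation heading should not count as evidence, and the point does not use it. It rests on an explicit rule in the Control group section that conflicts with the label. An unseen figure or analysis plan could add to that text but could not undo it.

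A reader might go further and infer that genetic risk does not overlap at all between the groups, so that the effect is fully confounded and no covariate model could help. The documents do not support this. The Control group section says that controls have a risk of 2 or less; it does not say that everyone at 2 or less is a control. The non-cancer group includes exercise-centre members and app-only users with no stated risk, and the Subject selection criteria recruit 300 centre members without a risk criterion. Low-risk exercisers are therefore possible. The Abstract points the other way by describing all 300 non-cancer participants as at elevated risk. Overlap is thus unclear rather than absent. Cancer status is different, because no cancer control is described anywhere.

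It is also fair to say that the rejection rates are hypothetical: neither the 320:80 split nor any value of b comes from the article.

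**Conclusion.** The point holds as a contradiction between a stated design property and a stated rule. As written, the exercise-versus-control contrast is confounded with genetic risk and with cancer status, and it cannot be read as the effect of the programme. For cancer patients, the group about whom the Discussion makes its main claims, there is no comparator at all as described.

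The size of the resulting bias is not known. Under the assumed 320:80 split with no true effect, false-positive rates run from about 13% for a 0.1 SD background difference to about 98% for 0.5 SD, against a nominal 5%. These figures show sensitivity and are not estimates for this trial. The contradiction itself needs none of these assumptions.

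**What to change.** Reconcile the Abstract, the randomisation paragraph, the Exercise interventions section and the Control group section, so that they state one rule for who exercises and who does not.

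**Minimum change.** Delete the word randomized from the Abstract and the Exercise interventions section, and from the registry entry if it says the same (it was not available here). Call the study a non-randomised controlled study, and withdraw the causal efficacy claims, including the Discussion's statements that the results will confirm effects. This costs a text amendment, possibly a registry amendment, and a less favourable design label.

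**If the sponsor wants to keep the label.** Participants still to be enrolled would have to be allocated at random, stratified by cancer status and genetic risk (2 or less, more than 2). Those already placed by genotype would be reported separately. This is not cheap. It needs ethics and consent amendments, and it makes some high-risk people and some cancer patients no-exercise controls. Because the study has been running since April 2024, it also leaves a randomised comparison smaller than 500, by a number the article does not allow one to work out.
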